#### Power Calculation

Due to the anticipated difficulties in recruitment that will likely arise from the complexities of running a study during a pandemic and the time-sensitive nature of implementing an early sleep intervention relative to both the start of the pandemic and insomnia symptoms, we view this trial as a feasibility study. Therefore, for this feasibility trial, we aimed to recruit a total of 50 subjects, which would result in 25 subjects in each study group. With this sample size, our power calculations were derived using the 2-group *t* test of equal means based on the difference between CBT-I and waitlist control group at 28 weeks, at a 5% level of significance. With 25 per group, the study is 80% powered to detect a large effect size (Cohen d=0.80).

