### Statistical Procedure and Data Analysis

Given the nature of this feasibility study, for all our analyses and interpretation, we will place a primary emphasis on estimation of effect sizes and confidence intervals rather than on testing statistical significance.

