#### Primary Analyses

Statistical analyses aim 1 is to determine whether a brief, telehealth CBT-I reduces insomnia symptoms arising during the COVID-19 pandemic. All primary analyses will be performed using the intention-to-treat principle. We will test whether CBT-I is superior to a waitlist control in reducing insomnia symptoms by using a mixed effects linear model with autoregressive error structure using intention-to-treat analysis with outcomes at time points 6, 12, and 28. Insomnia severity as measured by the ISI will be entered as the dependent variable with randomization group (2 levels), time point (weeks 0, 6, 12, and 28), and group-by-time interaction included as fixed effects. The model will also include a random slope. Several hypotheses (1.1a-d) will be tested using the described mixed effects model.

Hypothesis 1.1a is that individuals assigned to the CBT-I group will experience an improved trajectory of insomnia symptoms during the waitlist-controlled 28-week period relative to those assigned to the waitlist control group. This hypothesis will be tested using a likelihood ratio test of the coefficients of the time and group-by-time interaction of the aforementioned mixed effects linear model.

Hypotheses 1.1b-1.1d are that individuals assigned to the CBT-I group during the waitlist-controlled period will have lower insomnia symptoms compared with those assigned to the waitlist-control group immediately posttreatment (hypothesis 1.1b; week 6) and at the short-term (hypothesis 1.1c; week 12) and long-term (hypothesis 1.1d; week 28) follow-ups. These hypotheses will be tested using the aforementioned mixed effects linear model with independent likelihood ratio tests using the treatment coefficient for the posttreatment (hypothesis 1.1b; Δ_1_ in Figure 2), short-term (hypothesis 1.1c; Δ_2_ in Figure 2), and long-term (hypothesis 1.1c; Δ_3_ in Figure 2) follow-up time points.

We will also test whether CBT-I is superior to the waitlist control in preventing an insomnia diagnosis following treatment by using multiple logistic regression analysis.

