Hypotheses 1.2a and 1.2b are that individuals who were assigned to the CBT-I group will be less likely to have an insomnia diagnosis than those who were assigned to the waitlist control group at weeks 12 and 28. These hypotheses will be tested using 2 separate logistic regression models, one using the short-term (hypothesis 1.2a; 12 weeks) and one using long-term (hypothesis 1.2b; 28 weeks) follow-up insomnia diagnosis, as defined by the Duke, as the dependent variable, with treatment (CBT-I, waitlist) as the independent variable.

Statistical analyses aim 2 is to determine whether a brief, telehealth CBT-I improves well-being during the COVID-19 pandemic. We will test whether immediate CBT-I is superior to a waitlist control in improving depressive symptoms as the primary measure of well-being during the waitlist-controlled period (28-week duration) by using a mixed effects linear model with autoregressive error structure using intention-to-treat analysis. Depression severity, as assessed by the BDI-II, will be entered as the dependent variable with baseline covariates used for stratified randomization (ie, baseline insomnia severity and sex), group (immediate CBT-I or waitlist control), time point (weeks 0-6, 12, and 28), and group-by-time interaction included as fixed effects. The model will also include a random slope. Separate, secondary analyses will be conducted on the secondary measures relating to well-being described in the Secondary Outcomes section (eg, anxiety, suicidality, quality of life). Several hypotheses will be tested using this model.

Hypothesis 2.2a is that individuals assigned to the CBT-I group will have an improved trajectory of depressive symptoms across the 28 weeks relative to individuals assigned to the waitlist control group. This hypothesis will be tested using a likelihood ratio test of the coefficients of the time and group-by-time interaction terms of the aforementioned mixed effects linear model.

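### Hypotheses 1.1a and 2.2a claim an improved course under CBT-I, but the stated likelihood ratio test has no direction and, if time is a factor, gives no single effect estimate

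*Protocol article*

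**What the plan says.** Under Primary Analyses in the protocol article, hypothesis 1.1a says that the CBT-I group "will experience an improved trajectory of insomnia symptoms during the waitlist-controlled 28-week period" relative to the waitlist. Hypothesis 2.2a says that the CBT-I group "will have an improved trajectory of depressive symptoms across the 28 weeks relative to individuals assigned to the waitlist control group". Both are directional claims about a difference between arms.

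Both are tested in the same way, by a likelihood ratio test on the time coefficients and the group-by-time coefficients of a mixed model. The insomnia model (ISI) uses weeks 0, 6, 12 and 28. The depression model has "time point (weeks 0-6, 12, and 28), and group-by-time interaction included as fixed effects". Both models add a random slope. No sign condition and no summary contrast is attached to either hypothesis, and the coding of time (factor or numeric) is not given.

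The same models also supply separate tests of the treatment effect at weeks 6, 12 and 28 (1.1b-d and 2.2b-d).

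The opening of Statistical Procedure and Data Analysis places, for all analyses, a "primary emphasis on estimation of effect sizes and confidence intervals rather than on testing statistical significance".

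The depression model names the BDI-II as its outcome. Under Secondary Outcomes, the BDI-II falls among the measures taken at weeks 0, 12, 28 and 56 only. Under Primary Outcomes, the PHQ-9 is the primary depression measure and is also taken weekly.

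**The concern.** The hypothesis and its test do not match. A test that several coefficients are all zero rejects for any departure, whichever arm it favours and at whichever visits it occurs. It has no sign and no single estimate. An improved trajectory is a claim about sign and size, and the plan says that sizes and intervals are its main output. As written, 1.1a and 2.2a can be declared supported by a p-value that does not show which arm did better or by how much.

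The time coefficients sit in the same test. If they are tested jointly with the interaction, as the sentence reads, the test can also reject when both arms improve by the same amount.

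**Working it through.** **1. The plan's own power figure.** Power Calculation gives 80% for d = 0.80 with 25 per group, from a "2-group *t* test of equal means based on the difference between CBT-I and waitlist control group at 28 weeks", "at a 5% level of significance" (sidedness not stated; two-sided assumed). Check: 0.80 × √(25/2) = 2.828; 2.828 − 1.960 = 0.868; Φ(0.868) = 80.7%. The noncentral t with 48 df gives 79.1%. The figure reproduces, but it describes one comparison at week 28 and not the trajectory test.

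**2. Degrees of freedom of the group-by-time part.**
- Time linear: 1 df, one signed slope difference.
- Time a factor, ISI at four visits: 3 df.
- Time a factor, BDI-II as collected within 28 weeks (weeks 0, 12, 28): 2 df.
- Time a factor, weekly PHQ-9 at nine visits: 8 df.

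The listed visits and the separate effects at weeks 6, 12 and 28 point to a factor, because one straight line cannot give three free effects. The random slope needs numeric time, so the point stays open.

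**3. Direction.** Let δ be the vector of between-arm differences in change from week 0 and V its covariance. In Wald form the statistic is δ′V⁻¹δ. Replacing δ by −δ leaves it unchanged, so a benefit and its mirror-image harm are rejected equally often.

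**4. Size.** Assumptions: 25 per arm, SD 1, complete data, two-sided 5%. Power is from the noncentral F with k and 48 df and noncentrality λ = δ′V⁻¹δ, where V = (2/25)·CRC′, R is the correlation matrix and C takes changes from week 0. The documents give no correlations, so three structures are shown: S1, constant 0.5; S2, autoregressive 0.7 per visit; S3, 0.4 + 0.6 × 0.5^lag. The single contrast is the mean of the follow-up weeks minus week 0: weeks 6, 12 and 28, or weeks 12 and 28 for the BDI-II.

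Worked case (ISI, S1, benefit 0.8 held):
- Omnibus: λ = 0.64 × 3/(1 + 2 × 0.5) ÷ 0.08 = 12.0 on 3 df, power 81%.
- Contrast: variance 1 + 2/3 − 2 × 0.5 = 2/3, so λ = 0.64/(0.08 × 2/3) = 12.0 on 1 df, power 92%.

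| True between-arm pattern | df | Omnibus rejects, S1/S2/S3 | Single contrast rejects, S1/S2/S3 |
|---|---|---|---|
| ISI: benefit 0.8 at weeks 6, 12, 28 | 3 | 81/87/89% | 92/90/94% |
| BDI-II: benefit 0.8 at weeks 12, 28 | 2 | 82/90/92% | 89/93/95% |
| PHQ-9 weekly: benefit rising to 0.8 at week 6, then held | 8 | 83/26/46% | 92/60/81% |
| ISI: benefit 0.8, 0.4, 0.2 (waning) | 3 | 66/90/89% | 51/47/54% |
| ISI: CBT-I worse by 0.8 at week 6 only | 3 | 81/98/97% | 21/19/22%, with the adverse sign visible |
| PHQ-9 weekly: CBT-I worse by 0.4, 0.8, 0.8, 0.4, 0.2 at weeks 1-5, equal after | 8 | 90/61/72% | 5/5/5% |

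Sensitivity: with the 26 and 23 people randomised, three other correlation structures and a chi-square approximation, a held 0.8 benefit gives 91-92% against 94-96% (ISI) and 93-94% against 95-96% (BDI-II). The waning ISI pattern gives 90-93% against 54-58%.

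**5. Time terms in the same test.** Suppose both arms improve by 0.5 SD and do not differ. For the ISI under S1, λ = 2 × 25 × 0.25 × 1.5 = 18.75 on 6 df, and the joint test rejects in 92% (chi-square approximation); S2 and S3 give 96% and 97%. With nine visits (16 df, improvement reached by week 6) it rejects in 96/36/62%.

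**The case against.** **The time coding is inferred.** With linear time the interaction is one signed slope difference with its own interval, and most of the concern about direction and estimate falls away. An article may leave the coding to the full protocol or SAP. This stands as a limit on the point. It does not remove it: the article itself fixes hypothesis, model and test, asks the same model for separate effects at three weeks, and puts the time coefficients in the test under either coding.

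**Direction and estimates come from elsewhere in the plan.** The contrasts at weeks 6, 12 and 28 are signed, and the plan puts effect sizes first throughout. This largely stands. A reader might infer that a temporary worsening under CBT-I would be reported as an improved course. The documents do not support that as a general risk. For the ISI, the model has no visit between weeks 0 and 6, and a worsening at week 6 would show in 1.1b. The BDI-II is not collected at weeks 1-5, so an early worsening could not enter its model. Only with the weekly PHQ-9 could an effect confined to weeks 1-5 drive the test and escape all of 2.2b-d.

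**The power argument is weak.** A reader might also infer that the omnibus test would often miss a real benefit. Under a held benefit that is so only at 8 df, and the nine-visit schedule does not fit the BDI-II named in the model. A plateau is also the pattern that suits the average contrast. For a weekly outcome with a benefit of 0.4 SD at week 1, 0.8 at weeks 2-6, 0.2 at week 12 and none at week 28 (structure S3, 26 and 23 people, chi-square approximation), the 8-df test has 91% power and the average contrast 22%. This objection stands, so power is not the ground for the change.

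**Conclusion.** The point holds on direction and estimand. The stated test of 1.1a and 2.2a cannot by itself show that CBT-I improved the course. If time is a factor, the better-supported but unstated reading, it also gives no single effect size or interval, contrary to the plan's stated emphasis. The week-specific contrasts partly protect against misreading.

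The effect on power is secondary. Under a sustained 0.8 SD benefit the loss is about 3 to 12 points for the ISI, 2 to 8 points for the BDI-II as collected, and about 9 to 35 points only for a weekly depression score. It reverses when the benefit wanes. Apart from the reproduced 80%, all power figures rest on assumed correlations and effect shapes and on complete data, and they leave out the random slope. In a feasibility study that plays down significance testing, this is a worthwhile correction to the analysis text, not a threat to the trial.

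**What to change.** 1. State whether time is a factor or numeric in the fixed effects, and how the random slope is coded.
2. Base 1.1a and 2.2a on one prespecified signed between-arm contrast each, from the same mixed model, with estimate and 95% CI. One example is the difference in change from week 0 to the mean of the primary follow-up weeks at which the outcome is collected: weeks 6, 12 and 28 for the ISI or PHQ-9, weeks 12 and 28 for the BDI-II. Weeks 1-5 can stay in a weekly depression model as data without entering the contrast.
3. Report the group-by-time omnibus test, without the time main effects, as supportive, next to the week-specific contrasts.

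The cost is one paragraph of analysis text and no new data. Trial Status and Timeline reports interim analyses at week 6 but says that the primary hypotheses had not been tested in full, so the change should be dated. The downside is that an average is insensitive to effects that wane or reverse; the week-specific contrasts and the omnibus test still show these.

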Hypotheses 2.2b-2.2d are that individuals assigned to the CBT-I group will have lower depressive symptoms compared who those who were assigned to the waitlist control group immediately posttreatment (hypothesis 2.2b; week 6) and at the short-term (hypothesis 2.2c; week 12) and long-term (hypothesis 2.2d; week 28) follow-ups. These hypotheses will be tested using the aforementioned mixed effects linear model with independent likelihood ratio tests using the treatment coefficient for the posttreatment (hypothesis 1.2b; week 6), short-term (hypothesis 1.2c; week 12), and long-term (hypothesis 1.2c; week 28) follow-up time points.

Hypothesis 2.3 is that improvement in insomnia symptom severity (measured by the ISI) will mediate subsequent improvement in well-being from baseline (week 0) to posttreatment (week 6), short-term follow-up (week 12), and long-term follow-up (week 28). Using the approach described by Kraemer at al [61] and Manber et al [34], linear regression analyses will be used to determine whether change in the ISI score from Session 1 (week 1) to Session 4 (week 5) of treatment mediates the subsequent depressive symptom improvement (primary outcome measure) after the completion of treatment (week 6). Change in ISI score at Session 4 will be estimated as the slope of the regression line of ISI scores from Session 1 (week 1) through the treatment phase to Session 4 (week 6) using all available data from each participant. The model will include group (CBT-I or waitlist control), change in ISI score from Session 1 to Session 4 (participant specific slopes), and their interaction with depression severity, as measured by the PHQ-9, as the dependent variables. Mediation will be tested using the MacArthur approach as described by Kraemer et al [62]. Specifically, a mediation effect requires a significant effect of the intervention on the mediator (Path A in Figure 3) and a significant association between the mediator and the outcome (Path B in Figure 3).

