This study was conceived and launched in response to the global pandemic of COVID-19, which, while rendering it novel, presents unique challenges. First, to address our scientific questions, we sought to recruit participants early in the course of their sleep disturbance, causing a significant urgency to launch the study. This time pressure led us to conduct this study with limited resources, which impacted our recruitment efforts. We were unable to offer compensation for participation. We relied heavily on recruiting participants through free online platforms, such as social media posts, online message boards, and electronic newsletters. Due to these recruitment concerns and the resulting decreased statistical power for the planned analysis, we view this as a feasibility study. Therefore, the planned analyses and publications resulting from this protocol will utilize effect size estimates, rather than statistical significance, to provide pilot and feasibility data to inform future hypotheses. A second potential limitation is the unequal attrition rate in the treatment versus the waitlist control group. Since participants are not financially compensated, the primary motivation of participation is meeting with a therapist on a weekly basis to address their sleep concerns. Thus, it is possible that individuals in the waitlist control group were more likely to decline to participate in follow-up time points due to loss of interest or spontaneous improvement in symptoms over time. Although this could potentially affect the ability to detect significant differences in between-group comparisons at the long-term follow-up time points due to inadequate power, our analytic approach using regression models has the advantage of increased efficiency and power over unadjusted analyses [63,64]. We will address this issue by assessing whether missingness is related to any observed covariates. If this is the case, an issue of greater concern is the potential bias in the estimate of the treatment effect if neither the missing completely at random (MCAR) nor the missing at random (MAR) assumption holds. Although mixed effects linear models lead to unbiased estimates of the treatment effect under the MCAR and MAR assumptions, estimates may be biased under nonignorable missingness. Further sensitivity analyses will be performed if this is the case.

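### Hypothesis 2.3 makes mediation depend on two significant tests, against the plan's own emphasis on effect sizes and confidence intervals, so non-significance would be read as no mediation

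*Protocol article*

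**What the plan says.** Three places in the protocol article bear on this point.

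- **Statistical Procedure and Data Analysis, opening statement.** For every analysis and its interpretation, "we will place a primary emphasis on estimation of effect sizes and confidence intervals rather than on testing statistical significance". The reason given is that this is a feasibility study.
- **Discussion, limitations.** Recruitment problems and the resulting loss of power are named, and the planned analyses and publications "will utilize effect size estimates, rather than statistical significance, to provide pilot and feasibility data to inform future hypotheses".
- **Primary Analyses, aim 2, hypothesis 2.3.** PHQ-9 is regressed on group, each participant's ISI slope over the treatment weeks, and their interaction. The decision rule then reads: "a mediation effect requires a significant effect of the intervention on the mediator (Path A in Figure 3) and a significant association". The second condition is Path B, which links the ISI slope to PHQ-9. The text for this hypothesis names no indirect effect.

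The only power calculation (Power Calculation section) is for a group difference at week 28, "at a 5% level of significance", with 25 per group and d = 0.80. It does not address mediation.

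**The concern.** Two rules apply to one analysis. Suppose Path A is estimated as a large effect with p just above 0.05. Under the general rule the analyst reports the estimate and its interval and lets the uncertainty show. Under the hypothesis 2.3 rule the analyst must say that there is no mediation effect. The document does not say which rule prevails.

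This differs from the other tests in the same section. Hypotheses 1.1 and 2.2 also use likelihood ratio tests, but the models behind them give estimates that can be read under the estimation rule. Only hypothesis 2.3 makes significance a requirement for the effect to exist.

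What is at stake is the trial's mechanistic message. The Introduction says the findings will guide larger trials, and the Overall Design section stresses pathways between sleep and well-being. A finding of no mediation, drawn from two tests in a sample that the authors themselves regard as short of power, could steer later trials away from a pathway that was only imprecisely measured.

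**Working it through.** **1. The plan's own figure.** Inputs: n = 25 per group ("we aimed to recruit a total of 50 subjects, which would result in 25 subjects in each study group"), d = 0.80, 5% level; sidedness is not stated.

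Normal approximation: power = Φ(d·√(n/2) − 1.96) = Φ(0.8 × √12.5 − 1.96) = Φ(2.828 − 1.960) = Φ(0.868) = 80.7%. The exact two-sided t test gives 79.1% and a one-sided t test 87.4%. The stated 80% is reproduced as a two-sided calculation, so two-sided tests are used below.

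**2. Inputs for the mediation rule.**

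- Sample: 25 per group as planned, or the 38 participants with week 6 data (Trial Status and Timeline). The split of the 38 by arm is not given; 20/18 is assumed, with 19/19 as a check.
- Path A (arm difference in the mediator): not given. d = 0.8 is assumed as the main case, and 0.5, 1.0 and 1.2 are also tried.
- Path B (within-arm correlation r of mediator and outcome): not given; 0.3, 0.4 and 0.5 are assumed.
- Normal errors, no true interaction, no direct effect of arm, no baseline covariates.

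**3. Method.** Simulation with 6,000 trials per setting. Mediator = d × arm (coded ±½) + unit normal error. Outcome = [r/√(1 − r²)] × mediator + unit normal error. Path A is a t test of the mediator by arm. Path B is the mediator term in a regression on arm, centred mediator and their interaction. The rule is met when both p-values are below 0.05. The Monte Carlo standard error is at most √(0.25/6000) = 0.65 percentage points.

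**4. Results at d = 0.8.**

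| Sample | r | Path A significant | Path B significant | Both significant |
|---|---|---|---|---|
| 25/25 | 0.3 | 79.1% | 54.5% | 42.5% |
| 25/25 | 0.4 | 79.4% | 81.2% | 63.9% |
| 25/25 | 0.5 | 80.5% | 95.3% | 76.6% |
| 20/18 | 0.3 | 66.3% | 42.7% | 28.1% |
| 20/18 | 0.4 | 66.2% | 68.0% | 44.8% |
| 20/18 | 0.5 | 67.4% | 88.6% | 59.2% |

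The two tests are nearly independent, so the last column is close to the product of the two before it (20/18, r = 0.3: 0.663 × 0.427 = 0.283). A separate run with 19 per arm gave 27%, 46% and 59%. The chance that a true mediation effect is called absent is thus 41-73% with 38 completers (100 − 59 to 100 − 27) and 23-57% with 25 per arm (100 − 77 to 100 − 43).

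**5. Other Path A sizes** (both significant, for r = 0.3 / 0.4 / 0.5).

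| Path A d | 25/25 | 20/18 |
|---|---|---|
| 0.5 | 22 / 33 / 39% | 13 / 21 / 28% |
| 1.0 | 50 / 76 / 90% | 36 / 58 / 75% |
| 1.2 | 54 / 80 / 94% | 40 / 63 / 84% |

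Counting a significant interaction as Path B as well adds less than 3 points in any setting.

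**6. If Path A uses more participants than Path B.** ISI slopes are to use all available data, so Path A need not be limited to the 38. If all 49 randomised participants (26/23) gave a slope, Path A power at d = 0.8 would be 78.2%. Multiplying by Path B at 38 gives 0.782 × 0.427 = 33%, 0.782 × 0.680 = 53% and 0.782 × 0.886 = 69%, which lies between the two samples in step 4.

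**7. Is the two-test rule the cause of the low detection?** Percentile of trials in which a bootstrap 95% interval for the indirect effect (A × B) excludes zero, at d = 0.8 and Path B of 0.3 / 0.4 / 0.5 (1,500 trials, 500 resamples):

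| Per arm | Bootstrap interval | Two-test rule, same runs |
|---|---|---|
| 19 | 29 / 45 / 61% | 28 / 43 / 59% |
| 25 | 45 / 64 / 76% | 43 / 64 / 74% |

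The two are nearly equal. Sample size limits detection, not the choice between these two procedures.

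**The case against.** The strongest reply is that the general statement already covers hypothesis 2.3. It speaks of a primary emphasis, which leaves room for tests, and the Discussion commits the publications to effect sizes. On this view the mediation text merely repeats the criteria of the method it cites, and estimates with intervals would be reported anyway. The bootstrap comparison adds that the proposed interval would include zero about as often, so the change would yield no more information.

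Much of this stands. The general section does not abolish testing; a reader might infer that from the Discussion, but the two statements together support only a priority for estimation. The low detection rate follows from a sample size that the authors disclose. The absence of a named interval for hypothesis 2.3 would be no fault by itself, since a condensed article may leave that to the analysis plan.

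What does not stand is that the wording is therefore harmless. The mediation rule is fixed in this document, whatever its source, and it makes significance necessary for the effect to exist. An interval that includes zero still shows which indirect effects remain compatible with the data. A declaration of no mediation does not.

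Three stronger readings are tempting but unsupported. One is that true mediation would mostly be missed: detection is 64-77% with 25 per arm at d = 0.8 and r of 0.4 or more, and 59% with the 38 completers at r = 0.5. The second is that d = 0.80 is the plan's own Path A effect: it is the detectable week 28 difference, not an expected effect on an ISI slope over the treatment weeks. The third is that Path B would be tested in one arm only because of how arm is coded in the interaction model: the document states no coding.

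**Conclusion.** The point holds as an inconsistency with a practical consequence. The decision rule for hypothesis 2.3 conflicts with the estimation emphasis set for all analyses and repeated in the Discussion, and it would often turn an imprecise result into a finding of no mediation unless both paths are large.

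At an assumed Path A of d = 0.8 and Path B of 0.3 to 0.5, the rule is met in about 27-59% of trials with 38 completers and 43-77% with 25 per arm. These figures rest on assumed path sizes, an assumed split of completers, two-sided 5% tests and no true interaction. They show how far the rule's verdict depends on sample size; they are not a forecast for this trial. The defect is the inference drawn from non-significance, and it concerns this one hypothesis. The group comparisons under aims 1 and 2 are not affected.

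**What to change.** In the hypothesis 2.3 text, remove the requirement that both paths be significant. State instead that Path A, Path B, the group-by-slope interaction and the indirect effect (A × B) will each be reported as an estimate with a 95% confidence interval, by bootstrap for the indirect effect, and that no yes/no conclusion on mediation will be drawn. The cited mediation framework can stay as the description of the paths.

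The cost is a change of wording and a bootstrap run, with no new data. The one small loss is that the trial cannot make a binary mediation claim. The article reports that week 6 interim analyses had been done but that the primary hypotheses had not been tested in full, so the change should be dated, with a note on whether any mediation result had been seen by then.
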